# SAFETY DEFINITIONS AND REPORTING REQUIREMENTS

## 8.1 Adverse events (AEs)

### 8. 1. 1 Summary of known and potential risks of the study drug

*Cyclosporin A – side effects*

(according to http://medis.akhwien.at/cgi-bin/medisweb.exe?app_fach%20120689)

| **system** | **frequency** |  |
| --- | --- | --- |
| *blood, lymph system* | >1/1000, <1/100 | anemia, thrombocytopenia |
|  | >1/10000, <1/1000 | leukopenia, microangiopathic hemolytic anemia, hemolytic-uremic syndrome |
|  | >1/1000, <1/100 | menstruation dysorders |
|  | >1/10000, <1/1000 | hyperthermia, gynaecomastia, hot flushes |
| *metabolism* | >1/10 | hyperlipidemia |
|  | >1/100, <1/10 | anorexia, hyperuricemia |
|  | >1/1000, <1/100 | hyperkalemia, hypomagnesemia, weight gain, hyperglycemia |
| *nervous system* | >1/10 | tremor, head ache |
|  | >1/100, <1/10 | fatigue, parasthesia |
|  | >1/1000, <1/100 | signs of encephalopathy (e.g. convulsions, desorientation, sleeping disorders) |
|  | >1/10000, <1/1000 | motoric polyneuropathy |
|  | <1/1000 | deafness, papillary edema |
| *cardiovascular* | >1/10 | hypertension |
|  | >1/100, <1/10 | ischemic heart disease |
| *gastrointestinal* | >1/100, <1/10 | gingivitis hypertrophicans, gastrointestinal symptoms |
|  | >1/1000, <1/100 | gastric ulcera |
|  | >1/10000, <1/1000 | pancreatitis |
|  | <1/1000 | colitis |
| *liver, bile* | >1/1000, <1/100 | reversible increase of bilirubin and parameters of liver function |
| *skin* | >1/100, <1/10 | hypertrichosis |
|  | >1/1000, <1/100 | acne, rash |
|  | >1/10000, <1/1000 | redness, pruritus |
| *musculo-skeletal* | >1/100, <1/10 | seizures, muscle pain |
|  | >1/10000, <1/1000 | myopathy, weakness |
| *kidney, urinary tract* | >1/10 | increase of serum creatinine |

### 8. 1.2 Definition of adverse events

An AE is any adverse change from the subject's baseline condition, i.e., any unfavorable and unintended sign including an abnormal laboratory finding, symptom or disease which is considered to be clinically relevant be the physician that occurs during the course of the study, whether or not considered related to the study drug.

Adverse events include:

- Exacerbation of a pre-existing disease.
- Increase in frequency or intensity of a pre-existing episodic disease or medical condition.
- Disease or medical condition detected or diagnosed after study drug administration even though it may have been present prior to the start of the study.
- Continuous persistent disease or symptoms present at baseline that worsen following the start of the study.
- Lack of efficacy in the acute treatment of a life-threatening disease.
- Events considered by the investigator to be related to study-mandated procedures.
- Abnormal assessments, e.g., ECG and physical examination findings, must be reported as AEs if they represent a clinically significant finding that was not present at baseline or worsened during the course of the study.
- Laboratory test abnormalities must be reported as AEs if they represent a clinically significant finding, symptomatic or not, which was not present at baseline or worsened during the course of the study or led to dose reduction, interruption or permanent discontinuation of study drug.

Adverse events do not include:

- Medical or surgical procedure, e.g., surgery, endoscopy, tooth extraction, transfusion. However, the event leading to the procedure is an AE. If this event is serious, the procedure must be described in the SAE narrative.
- Pre-existing disease or medical condition that does not worsen.
- Situations in which an adverse change did not occur, e.g., hospitalizations for cosmetic elective surgery or for social and/or convenience reasons.
- Overdose of either study drug or concomitant medication without any signs or symptoms. However, overdose must be mentioned in the Study Drug Log.

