## 8. 3 Severity of adverse events

The severity of clinical AEs is graded on a three-point scale: mild, moderate, severe, and reported on specific AE pages of the CRF.

If the severity of an AE worsens during study drug administration, only the worst intensity should be reported on the AE page. If the AE lessens in intensity, no change in the severity is required.

If an AE occurs during a washout or placebo run-in phase and afterwards worsens during the treatment phase, a new AE page must be filled in with the intensity observed during study drug administration.

- **Mild**

Event may be noticeable to subject; does not influence daily activities; the AE resolves spontaneously or may require minimal therapeutic intervention;

- **Moderate**

Event may make subject uncomfortable; performance of daily activities may be influenced; intervention may be needed; the AE produces no sequelae.

- **Severe**

Event may cause noticeable discomfort; usually interferes with daily activities; subject may not be able to continue in the study; the AE produces sequelae, which require prolonged therapeutic intervention.

A mild, moderate or severe AE may or may not be serious. These terms are used to describe the intensity of a specific event (as in mild, moderate, or severe myocardial infarction). However, a severe event may be of relatively minor medical significance (such as severe headache) and is not necessarily serious. For example, nausea lasting several hours may be rated as severe, but may not be clinically serious. Fever of 39°C that is not considered severe may become serious if it prolongs hospital discharge by a day. Seriousness rather than severity serves as a guide for defining regulatory reporting obligations.

**8. 4** Relationship to study drug

For all AEs, the investigator will assess the causal relationship between the study drug and the AE using his/her clinical expertise and judgment according to the following algorithm that best fits the circumstances of the AE:

- Unrelated
  - May or may not follow a reasonable temporal sequence from administration of the study product
  - Is biologically implausible and does not follow known response pattern to the suspect study drug (if response pattern is previously known)
  - Can be explained by the known characteristics of the subject’s clinical state or other modes of therapy administered to the subject.
- Possible related
  - Follows a reasonable temporal sequence form administration of the study drug.

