### 10. 4. 3 Safety and tolerability endpoints

Safety and tolerability endpoints will be reported by use of descriptive statistics. Their relevance will be assessed from a clinical perspective.

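### The adverse-event definition in Section 8.1.2 makes the unblinded physician's undefined view of clinical relevance a condition for recording, which conflicts with the rest of Section 8 and may under-record new mild symptoms

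*Protocol*

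**What the plan says.** Section 8.1.2 of the protocol opens broadly: "An AE is any adverse change from the subject's baseline condition". The same sentence then explains this as an unfavourable sign (abnormal laboratory findings included), "symptom or disease which is considered to be clinically relevant be the physician that occurs during the course of the study", whether or not it is thought related to the drug. Relevance is not defined.

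The inclusion list that follows is mixed. Four bullets carry no relevance or significance condition: exacerbation of an existing disease, increased frequency or intensity of an episodic condition, disease newly detected after dosing, and "Continuous persistent disease or symptoms present at baseline that worsen following the start of the study". Two bullets do carry one. Abnormal assessments, with ECG and physical examination findings as the examples, count only when clinically significant and either new or worse than at baseline. For laboratory results the text is "Laboratory test abnormalities must be reported as AEs if they represent a clinically significant finding, symptomatic or not", again if new or worsened, or if the abnormality led to a change in study drug.

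Section 8.3 defines the mild grade: "Event may be noticeable to subject; does not influence daily activities; the AE resolves spontaneously or may require minimal therapeutic intervention". Section 8.5 requires the severity, mild included, to be entered in the case report form. Section 10.4.3 reports safety and tolerability endpoints descriptively.

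**The concern.** The definition decides what reaches the case report form. On its plain reading, a symptom that the treating physician thinks irrelevant is not an adverse event and need not be written down. That physician knows the treatment, since the synopsis describes an open study in one group and blinding is stated as not applicable. Two investigators could also record different events under the same sentence, because nothing says what relevant means.

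What is at stake is the absolute count of minor symptoms. There is no comparator arm against which a shortfall would show, and no later analysis can restore events that were never collected. For the same reason an analysis plan could not repair it.

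**Working it through.** The protocol states no figure on this point, so there is nothing to reproduce. The check compares the texts and then gives an illustration of scale.

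**1. Consistency of the definition**

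| Place | Condition for a symptom or disease to count |
| --- | --- |
| 8.1.2, opening clause | none: any adverse change from baseline |
| 8.1.2, rest of the same sentence | relevant in the physician's view, undefined |
| 8.1.2, first four inclusion bullets named above | none |
| 8.1.2, abnormal assessments and laboratory bullets | clinically significant, and new or worsened |
| 8.3 and 8.5 | mild events are graded and entered |

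If relevance were meant as a general condition, the separate significance condition in the two test-related bullets would be largely redundant. If it were not meant so, the lead sentence is wrong. Either way the section does not give one rule.

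**2. Which effects are exposed**

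Section 8.1.1 lists five effects of cyclosporine A at more than 1/10: hyperlipidemia, tremor, headache, hypertension and increased serum creatinine. The biochemical table schedules lipids and creatinine at every visit, and the visit schedule has blood pressure at every visit. Three of the five are therefore captured as data whatever the adverse-event judgement. Headache has no scheduled assessment. Tremor could be seen at a physical examination, but that is scheduled only at screening and at the end of study (or premature end of study). For these two, the adverse-event page is the main record.

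**3. Illustration of scale**

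Inputs: n = 30 or 50 patients (synopsis and sample size section). True incidence p = 10%, the lower edge of the class of more than 1/10, or 20% as a wider value; both are assumptions for this population. Share recorded f = 1, 0.5 or 0.25, also assumed; the protocol gives none.

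Expected recorded cases = n × p × f. Chance that none is recorded = (1 − p × f)^n.

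| n | p | f | Expected | Chance of none |
| --- | --- | --- | --- | --- |
| 30 | 0.10 | 1 | 3.0 | 0.90^30 = 0.042 |
| 30 | 0.10 | 0.5 | 1.5 | 0.95^30 = 0.215 |
| 30 | 0.10 | 0.25 | 0.75 | 0.975^30 = 0.468 |
| 50 | 0.10 | 1 | 5.0 | 0.90^50 = 0.005 |
| 50 | 0.10 | 0.5 | 2.5 | 0.95^50 = 0.077 |
| 50 | 0.10 | 0.25 | 1.25 | 0.975^50 = 0.282 |

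At p = 20% the expected counts double: 6.0 and 3.0 in 30 patients, and 10.0 and 5.0 in 50, for f = 1 and 0.5. The shortfall is driven entirely by f. The table shows sensitivity to the condition and does not estimate a bias.

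**The case against.** The relevance clause might attach to disease alone and leave signs and symptoms free. That reading is weak. The clause that follows it, on occurrence during the study, must govern all three nouns, and the relevance clause stands in the same position. An ambiguous reach would itself be a reason to rewrite the sentence.

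A better objection is that relevant does not mean moderate or severe, and that Sections 8.3 and 8.5 expressly provide for mild events, so an investigator who reads the whole of Section 8 would probably record many of them. This stands. It limits the point to a possible gap for new minor symptoms.

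A reader might infer more than the protocol supports:

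- That mild effects are in fact under-counted. The documents do not show this. They show a rule that permits it.
- That the most frequent effects are mostly mild and subjective. The protocol's list assigns no severity, and three of the five commonest effects are measured on schedule.
- That Section 10.4.3 defers the judgement of each event to the report. It says "Their relevance will be assessed from a clinical perspective", but this refers to the endpoints, and the only safety endpoint that the synopsis names is the glomerular filtration rate.
- That serious adverse events are filtered too, because Section 8.2 builds them on the definition of an adverse event. This is formal only. No realistic reading would call death, a threat to life or hospitalization irrelevant.
- That every clinical sign should lose its condition. The abnormal-assessments bullet attaches clinical significance to physical examination findings, so removing it for all signs would create a new contradiction.

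It is also true that no between-arm comparison or hypothesis test rests on adverse-event counts.

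**Conclusion.** The inconsistency is real and lies within Section 8. An undefined judgement by an unblinded physician is made a condition for recording, against the opening of the same sentence, four of the inclusion bullets and the mild grade. The consequence is a possible under-recording, of unknown size, of new mild symptoms that have no regular scheduled measurement. Only absolute counts of such symptoms are exposed. Laboratory values, blood pressure, glomerular filtration rate and the primary HCV-RNA analysis are untouched. The illustrated counts rest on assumed incidences and assumed recording shares. This is a cheap improvement to the wording and does not threaten the trial's main conclusion.

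**What to change.** In Section 8.1.2, remove the clinical-relevance condition from the lead sentence for symptoms, diseases and signs that the patient reports or that are observed spontaneously, so that every unfavourable change from baseline is recorded and graded under Section 8.3. Keep clinical significance as the condition only for laboratory findings and for abnormal assessments (ECG and physical examination findings), as the last two inclusion bullets state. The lead sentence and the bullets then give one rule.

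The cost is one changed sentence in the protocol and somewhat more minor entries on the adverse-event pages. No analysis or sample size changes.

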## 8. 2 Serious adverse events (SAEs)

A Serious Adverse Event (SAE) is defined by the International Conference on Harmonization (ICH) guidelines as any AE fulfilling at least one of the following criteria:

- results in deaths.
- Life-threatening – defined as an event in which the subject was, in the judgment of the investigator, at risk of death at the time of the event; it does not refer to an event that hypothetically might have caused death had it been more severe.
- Requiring subject's hospitalization or prolongation of existing hospitalization – inpatient hospitalization refers to any inpatient admission, regardless of length of stay.
- Resulting in persistent or significant disability or incapacity (i.e., a substantial disruption of a person’s ability to conduct normal life functions).
- Congenital anomaly or birth defect.
- Is medically significant or requires intervention to prevent at least one of the outcomes listed above.

Life-threatening refers to an event in which the subject was at risk of death at the time of the event. It does not refer to an event that hypothetically might have caused death if it were more severe.

Important medical events that may not immediately result in death, be life-threatening, or require hospitalization may be considered as SAEs when, based upon appropriate medical judgment, they may jeopardize the subject and may require medical or surgical intervention to prevent one of the outcomes listed in the definitions above.

### 8. 2. 1 Hospitalization – Prolongation of existing hospitalization

Hospitalization is defined as an overnight stay in a hospital unit and/or emergency room.

An additional overnight stay defines a prolongation of existing hospitalization.

The following is not considered an SAE and should be reported as an AE only:

- Treatment on an emergency or outsubject basis for an event not fulfilling the definition of seriousness given above and not resulting in hospitalization.

The following reasons kfor hospitalizations are not considered AEs, and therefore not SAEs:

- Hospitalizations for cosmetic elective surgery, social and/or convenience reasons.
- Standard monitoring of a pre-existing disease or medical condition that did not worsen, e.g., hospitalization for coronary angiography in a subject with stable angina pectoris.
- Elective treatment of a pre-existing disease or medical condition that did not worsen, e.g., hospitalization for chemotherapy for cancer, elective hip replacement for arthritis.

**8.2.2** SAEs related to study-mandated procedures

Such SAEs are defined as SAEs that appear to have a reasonable possibility of causal relationship (i.e., a relationship cannot be ruled out) to study-mandated procedures (excluding administration of study drug) such as discontinuation of subject's previous treatment during a washout period, or complication of a mandated invasive procedure (e.g., blood sampling, heart catheterization), or car accident on the way to the hospital for a study visit, etc.

### 8. 2. 3 Suspected unexpected serious adverse reactions (SUSARs)

SUSARs are all suspected adverse reactions related to the study drug that are both unexpected (not previously described in the SmPC - Summary of Product Characteristics or Investigator’s brochure) and serious.

**8.2.4. Pregnancy**

Any pregnancy that occurs during study participation must be reported to the principal investigator/sponsor. **To ensure subject safety, each pregnancy must be reported to the principal investigator/sponsor immediately** The pregnancy must be followed up to determine outcome (including premature termination) and status of mother and child. Pregnancy complications and elective terminations for medical reasons must be reported as an AE or SAE. Spontaneous abortions must be reported as an SAE.

Any SAE occurring in association with a pregnancy, brought to the investigator’s attention after the subject has completed the study and considered by the investigator as possibly related to the investigational product, must be promptly reported to the principal investigator/sponsor.

In addition, the investigator must attempt to collect pregnancy information on any female partners of male study subjects who become pregnant while the subject is enrolled in the study. Pregnancy information must be reported to the principal investigator/sponsor as described above.

Address of Sponsor:

Univ.-[name]. [name], Medical University of Vienna, Department of Internal Medicine III, Division of Nephrology and Dialysis, [name]

Address of Investigator:

Univ.-[name]. [name], Medical University of Vienna, Department of Internal Medicine III, Division of Nephrology and Dialysis, [name]

## 8. 3 Severity of adverse events

The severity of clinical AEs is graded on a three-point scale: mild, moderate, severe, and reported on specific AE pages of the CRF.

If the severity of an AE worsens during study drug administration, only the worst intensity should be reported on the AE page. If the AE lessens in intensity, no change in the severity is required.

If an AE occurs during a washout or placebo run-in phase and afterwards worsens during the treatment phase, a new AE page must be filled in with the intensity observed during study drug administration.

- **Mild**

Event may be noticeable to subject; does not influence daily activities; the AE resolves spontaneously or may require minimal therapeutic intervention;

- **Moderate**

Event may make subject uncomfortable; performance of daily activities may be influenced; intervention may be needed; the AE produces no sequelae.

- **Severe**

Event may cause noticeable discomfort; usually interferes with daily activities; subject may not be able to continue in the study; the AE produces sequelae, which require prolonged therapeutic intervention.

A mild, moderate or severe AE may or may not be serious. These terms are used to describe the intensity of a specific event (as in mild, moderate, or severe myocardial infarction). However, a severe event may be of relatively minor medical significance (such as severe headache) and is not necessarily serious. For example, nausea lasting several hours may be rated as severe, but may not be clinically serious. Fever of 39°C that is not considered severe may become serious if it prolongs hospital discharge by a day. Seriousness rather than severity serves as a guide for defining regulatory reporting obligations.

**8. 4** Relationship to study drug

For all AEs, the investigator will assess the causal relationship between the study drug and the AE using his/her clinical expertise and judgment according to the following algorithm that best fits the circumstances of the AE:

- Unrelated
  - May or may not follow a reasonable temporal sequence from administration of the study product
  - Is biologically implausible and does not follow known response pattern to the suspect study drug (if response pattern is previously known)
  - Can be explained by the known characteristics of the subject’s clinical state or other modes of therapy administered to the subject.
- Possible related
  - Follows a reasonable temporal sequence form administration of the study drug.
  - May follow a known response pattern to the study drug (if response pattern is previously known).
  - Could not be reasonable not be reasonably explained by the known characteristics of the subject’s clinical state or other modes of therapy administered to the subject, if applicable.
- Definitely related
  - Follows a reasonable temporal sequence form administration of the study drug.
  - Follows a known response pattern to the study drug (if response pattern is previously known).
  - No other reasonable cause is present.

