## 8. 5 Reporting procedures

A special section is designated to adverse events in the case report form. The following details must thereby be entered:

- Type of adverse event
- Start (date and time)
- End (date and time)
- Severity (mild, moderate, severe)
- Serious (no / yes)
- Unexpected (no / yes)
- Outcome (resolved, ongoing, ongoing – improved, ongoing – worsening)
- Relation to study drug (unrelated, possibly related, definitely related)

Adverse events are to be documented in the case report form in accordance with the above mentioned criteria.

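### Section 8.3 says AE severity means intensity but separates moderate from severe by sequelae, contradicting its own examples; the outcome list in 8.5 has no code for sequelae or death

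*Protocol*

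**What the plan says.** Protocol section 8.3 grades clinical adverse events on a three-point scale and states the purpose of the grades: "These terms are used to describe the intensity of a specific event". The definitions are as follows.

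- Mild: "Event may be noticeable to subject; does not influence daily activities; the AE resolves spontaneously or may require minimal therapeutic intervention".
- Moderate: some discomfort and a possible effect on daily activities, then "intervention may be needed; the AE produces no sequelae".
- Severe: noticeable discomfort and usual interference with daily activities, then "subject may not be able to continue in the study; the AE produces sequelae, which require prolonged therapeutic intervention".

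For an event that worsens on study drug, "only the worst intensity should be reported on the AE page". The closing paragraph distinguishes severity from seriousness by example: "However, a severe event may be of relatively minor medical significance (such as severe headache) and is not necessarily serious", and "For example, nausea lasting several hours may be rated as severe, but may not be clinically serious".

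Section 8.5 makes severity a required entry on the case report form. The outcome entry is: "Outcome (resolved, ongoing, ongoing – improved, ongoing – worsening".

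**The concern.** A severity grade should record how bad an event was, and an outcome code should record how it ended. Section 8.3 mixes the two. It announces an intensity scale but draws its one firm boundary, between moderate and severe, by what the event leaves behind. Someone who applies the definitions and someone who follows the examples can then give the same event different grades.

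Section 8.5 does not make up for this. Sequelae enter the severity grade, where they do not belong, and have no code in the outcome field, where they do.

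The trial has one group and reports safety descriptively (section 10.4.3), so no comparator arm is graded with the same ambiguity. Severity and outcome are fixed when the form is completed. An analysis plan cannot later recover an intensity that was graded by outcome, or a sequela that was never coded.

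**Working it through.** No arithmetic applies, and the plan gives no figure to reproduce. The check sets the parts of sections 8.3 and 8.5 side by side.

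**Step 1: which descriptors separate moderate from severe?**

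| Descriptor | Moderate | Severe | Firm boundary? |
| --- | --- | --- | --- |
| Discomfort | possible | possible, noticeable | No, both hedged |
| Daily activities | may be affected | usually affected | No, the two overlap |
| Treatment | may be needed | prolonged, but tied to sequelae | Not on its own |
| Continuing in the study | not mentioned | may be impossible | No, hedged |
| Sequelae | none | present | Yes, unhedged and mutually exclusive |

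Sequelae are the only categorical difference.

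**Step 2: apply the definitions to an intense event that resolves fully.** Take a headache or several hours of nausea that stops the patient's normal activities and leaves nothing behind.

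- Mild fails, because daily activities are affected.
- Severe fails on the sequelae clause, if that clause is read as a requirement.
- Moderate fits.

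**Step 3: compare with the examples.** The examples present a headache of minor medical significance and hours of nausea as possible severe events. Neither example says outright that there are no sequelae. However, short-lived nausea, or an event of minor medical significance, can hardly be one that leaves sequelae needing prolonged treatment. The definitions give moderate and the examples give severe. The fever and myocardial infarction examples in the same paragraph do not conflict with the definitions.

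**Step 4: compare with the worst-intensity rule.** Worst intensity is known at the peak of the event. Sequelae are known only afterwards. A grade that turns on sequelae does not record peak intensity, which is what the rule asks for.

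**Step 5: look for sequelae and death in section 8.5.** The outcome list has one code for resolution and three for ongoing events. Resolution with sequelae has no code, so sequelae of a non-serious event are not recorded as an outcome. A fatal event has no valid code on the AE page. Deaths are not lost to the trial: section 8.2 makes death a criterion for a serious adverse event, and section 8.5.1 requires a written report giving the event and its outcome.

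**The case against.** The strongest defence is that section 8.3 never says that every descriptor of a grade must be met. Most are hedged, and the closing paragraph tells the investigator that hours of nausea can be severe. Someone who reads the whole section can therefore grade by intensity. The trial is also single-centre, which limits disagreement between graders. This stands as a limit on the consequence. It does not remove the conflict, because the reader must set aside an unhedged clause in order to follow the examples.

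Several stronger readings are tempting, and the protocol does not support them.

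- *No fully resolved event can ever be severe.* This holds only if all descriptors are mandatory, which the text does not state.
- *Three to five patients per symptom would be misgraded.* Tremor and headache are listed as more frequent than 1/10, and 0.10 × 30 = 3 and 0.10 × 50 = 5. Those would be patients with the symptom, not patients with an intense, resolved and misgraded event. The listing gives no severity and no exposure period.
- *The severity table is the trial's safety result.* The synopsis names only glomerular filtration rate as the tolerability and safety endpoint, and section 10.4.3 specifies no severity table.
- *A symptom-free event with lasting damage fits no grade.* The definition of mild also expects spontaneous resolution or minimal treatment. Damage that needs prolonged treatment fails that and fits severe.

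It is also fair to say that no decision rule in the protocol uses the grade. Regulatory reporting follows seriousness. Study-drug discontinuation rests on the patient's interest, defined falls in GFR or serious side effects.

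**Conclusion.** The point holds as an internal contradiction in section 8.3 and a gap in the outcome codes of section 8.5. On a literal reading, an intense event that interferes with daily activities and leaves no sequelae is graded moderate. That disagrees with two of the section's own examples and with its worst-intensity rule.

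The size is modest. Grading may be inconsistent or too low in descriptive adverse-event data, and the number of events affected is unknown and could be zero. The primary HCV-RNA analysis, the sample size and regulatory reporting are unaffected.

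The conclusion rests on two assumptions: that staff may reasonably treat the unhedged sequelae clauses as binding, and that the headache and nausea in the examples leave no sequelae. The case report form is an appendix that was not available, so the statement about outcome codes rests on the list in section 8.5.

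**What to change.** 1. In section 8.3, remove the sequelae clause from moderate and the clause on sequelae and prolonged treatment from severe. Deletion alone would leave a thin boundary, so sharpen the remaining wording so that the two grades differ by degree of discomfort and interference with daily activities. For example: moderate, daily activities may be influenced; severe, the event prevents or markedly interferes with daily activities.
2. In section 8.5, and on the AE page if it carries the same list, add *resolved with sequelae* and *fatal* to the outcome codes.

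The cost is two clauses removed, one boundary reworded and two codes added. AE pages already completed would need a check of severity grade and outcome code against the revised text.
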